##### Longitudinal audio diaries (LADs)

3.2.2.2.

A subset of participants will keep an approximate five-minute, fortnightly longitudinal audio diary (LAD) account of their experience of their dietary intervention over the 24-week period. LADs have been found to be a flexible and useful tool for enriching qualitative data collected on experiences over time that can be context specific (33). LADs allow participants to reflect on experiences at the time of the experience, rather than relying on recall as is typically the process of standard in-depth interviewing (33). In addition, it has been suggested that participants may more freely disclose matters of personal salience without the presence of a researcher (33).

The aim of the LADs is to capture the participant’s experience of their allocated dietary intervention each fortnight, in particular what has worked or not worked for aspects of food consumption and the enablers or barriers thought to have influenced this experience. Participants will be encouraged to use their mobile/smart phone to record their diary, or will be provided with an alternative option if preferred. An audio diary prompt sheet will be provided to participants with questions to consider (see Supplementary material 2), which has been designed in accordance with previous research using this method as an evaluation tool (34). A practice session with their mobile phone/recorder will be undertaken at the end of the first interview to ensure participants are able to use the technology. The audio diaries will be transcribed verbatim by the main researcher (CD) or a transcription service. After listening to the audio diary, if issues of concern are raised, such as participant discomfort, this will be discussed with the wider research team for appropriate next steps and escalation if required.

##### Researcher reflexivity

3.2.2.3.

Researcher reflexivity is an important component to allow for an awareness of how a researcher’s positionality may influence the research process, and to provide transparent and high-quality qualitative research (35, 36). The main researcher (CD) is an accredited practising dietitian undertaking this work as part of her PhD studies and has experience in both quantitative and qualitative research methods. CD will be involved in the wider SWIFt study as a researcher collecting data and as a study dietitian undertaking dietary consults with SWIFt participants. Reflexive diaries will be completed by the main researcher at key data points along the research process, including: after each participant interview, after reviewing participant LADs, and at each step of the data analysis process. Insights into this process will be discussed, as appropriate, at fortnightly meetings with the wider researcher team. This will allow documentation of key steps to the data collection and analysis process that can be reported as part of study results, adding transparency to the research process.

### Data analysis

3.3.

Quantitative data on participant engagement (see Objective 1 at Table 1) will be analyzed for frequency/count and proportions or as overall daily energy restriction as described above. Regression models will be used to examine associations between engagement measures, participant characteristics (sex, age, ethnicity, occupation, shift schedule, number of night shifts per fortnight, years in night shift), intervention group, and weight change. It is anticipated that general linear regression models will be used for dependent variables that are continuous data and generalized linear regression models will be used for dependent variables that are count data. Differences in drop-out/time to drop out between intervention groups will be examined via survival curve analysis.

Qualitative data includes interview transcripts and longitudinal audio diary transcripts and will be entered into NVivo (qualitative research computer software; Version 12) and analyzed using the five-steps of “framework analysis” (37, 38). In step one (*familiarization*), a subset of transcripts representing a mix of dietary intervention groups will be analyzed inductively by one researcher (CD) and reviewed by another researcher (SK) to identify influencing factors (intervention features in addition to enablers and barriers) for participant engagement for the allocated dietary intervention. Step two (*identifying a thematic framework*) involves developing an initial coding framework based on step one that details coding for the influencing factors for participant engagement. This step will also map enablers and barriers to the domains of the social-ecological model (SEM) (19) as a guide for developing themes and sub-themes. The SEM consists of five distinct domains (individual, social, organisational, community, public policy) and considers how these factors interact to influence health behaviours, enabling the development of strategies to improve behaviours. In step three (*indexing*), the framework will be used to code all data in NVivo. The Theoretical Domains Framework (TDF; described previously) (31) and the behaviour change taxonomy (BCT) (39) for intervention features, will also be used to map themes and sub-themes. The BCT is a set of 93 distinct behaviour change techniques that describe the components of an intervention thought to drive behaviour change (39). Where themes do not appear to fit within the mentioned frameworks, additional theoretical frameworks [e.g., Behaviour Change Wheel (BCW)] may be incorporated as necessary. In step four (*charting*), any differences between the dietary interventions and participant characteristics will be identified.

Finally, step five (*mapping and interpretation*) involves interpreting the findings based on existing literature. Merging of the qualitative and quantitative data (side-by-side comparison method) (40) will also be undertaken at this stage (see last two analysis steps at Figure 1). Qualitative themes will be used to help explain any associations found between engagement measures, participant characteristics, intervention group, and weight change from the quantitative data. This will be undertaken in both table and narrative form to assist in interpretation. Results from the different data sources will be integrated to confirm or refute the findings of each data source and to interrogate the validity of conclusions.

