**Methods:**

A convergent, mixed-methods evaluation design was chosen where quantitative and qualitative data collection occurs concurrently, analyzed separately, and converged in a final synthesis. Quantitative measures include participant engagement assessed via: dietary consult attendance, fulfillment of dietary goals, dietary energy intake, adherence to self-monitoring, and rates for participant drop-out; analyzed for frequency and proportions. Regression models will determine associations between engagement measures, participant characteristics (sex, age, ethnicity, occupation, shift type, night-shifts per week, years in night shift), intervention group, and weight change. Qualitative measures include semi-structured interviews with participants at baseline, 24-weeks, and 18-months, and fortnightly audio-diaries during the 24-week intervention. Interviews/diaries will be transcribed verbatim and analyzed using five-step thematic framework analysis in NVivo. Results from the quantitative and qualitative data will be integrated via table and narrative form to interrogate the validity of conclusions.

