### Participants

3.1.

Eligibility criteria and recruitment for the overall SWIFt study has been previously described (11). In summary, study participants will be aged between 25 and 65 years and working a minimum of two nights per week for a minimum of six consecutive months. Participants will have a body mass index (BMI) of ≥28 kg/m^2^ for non-Asian men and women and ≥ 26 kg/m^2^ for Asian men and women and be able to attend either study site. Please refer to the previously published study protocol for exclusion criteria relating to medical and lifestyle conditions that may affect body composition, metabolism, or ability to follow the dietary protocol (11). Participants who consent to be invited to complete longitudinal audio diaries (LADs) and/or semi-structured interviews will be contacted after randomization based on a maximum-variation sampling approach (23). Maximum variation is used to provide a diverse set of participant viewpoints across age, sex, occupation, shift-type, and intervention group. Participants who discontinue with the intervention will also be invited for an interview. Identifying sample size *a priori* for qualitative research is problematic (24), therefore data collection and preliminary data analysis will occur concurrently, and recruitment will cease once maximum-variation is met, and when limited new information is identified.

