2.2 Contextual features.	Relationship between participant characteristics* and engagement measures (1.1, 1.2, 1.3, 1.4, 1.5). Participant reasons for drop-out.	Semi-structured interviews. Longitudinal audio diaries (LADs). Enablers/barriers to engagement mapped to the SEM.
3. Explore for who weight change outcomes are achieved for each of the SWIFt weight loss interventions and the influence of participant engagement.		
3.1 Intervention features.	Relationship between weight outcome and engagement measures (1.1, 1.2, 1.3, 1.4).	Participant interviews. Longitudinal audio diaries (LADs). Features of intervention mapped to the BCT and TDF.
3.2 Contextual features.	Relationship between participant characteristics* and weight outcome (24-weeks and 18-months).	Participant interviews. Longitudinal audio diaries (LADs). Enablers/barriers to outcomes mapped to the SEM.

^*^Participant characteristics include: age, sex, ethnicity, occupation, shift schedule, number of night shifts per fortnight; years in night shift; BCT, Behaviour Change Taxonomy; TDF, Theoretical Domains Framework; SEM, Social-Ecological Model.

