##### Other SWIFt study quantitative data sources

3.2.1.6.

Other SWIFt study data sources to be used for this evaluation have been described previously as part of the wider SWIFt study protocol (11) and include: weight at baseline, 24-weeks and 18-months; demographics and socioeconomic factors at baseline [age, sex, ethnicity (28), occupation, shift schedule, number of night shifts per fortnight, years in night shift]. See Objectives 2 and 3 in Table 1.

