## Ethics and dissemination

5.

This mixed-methods evaluation protocol was approved by Monash Health Human Research Ethics Committee (RES 19-0000-462A) and registered with Monash University Human Research Ethics Committee. Ethical approval has also been obtained from the University of South Australia (HREC ID: 202379) and Ambulance Victoria Research Committee (R19-037). Consent to participate in both the quantitative and qualitative parts of the study was sought before data collection. Personal information (name and contact details) will be collected by study researchers and stored separately to research data in a password protected electronic database. Only the study’s researchers will have access to this information. All methods will be performed in accordance with the relevant guidelines and regulations of the approving ethics committees. Results from this evaluation will be disseminated via peer-reviewed journals, conference presentations, student theses, and presentations to interested workplaces that include shift workers.

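### Baseline weight is missing from the listed predictors of weight change and the outcome scale (kg or percent) is not stated, so sex and ethnicity associations may partly reflect starting body size

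*Protocol article*

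**What the plan says.** Section 3.3 (Data analysis) names the variables whose associations will be examined: the engagement measures, "participant characteristics (sex, age, ethnicity, occupation, shift schedule, number of night shifts per fortnight, years in night shift), intervention group, and weight change". The footnote to Table 1 gives the same seven characteristics: "Participant characteristics include: age, sex, ethnicity, occupation, shift schedule, number of night shifts per fortnight; years in night shift". The abstract has nearly the same list, but with shift type in place of shift schedule and nights counted per week: "participant characteristics (sex, age, ethnicity, occupation, shift type, night-shifts per week, years in night shift), intervention group, and weight change". Section 3.2.1.6 repeats the seven. None of the four places lists baseline weight or baseline BMI as a characteristic.

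Baseline weight is nevertheless at hand. Section 3.2.1.6 opens its list of data sources with "weight at baseline, 24-weeks and 18-months; demographics and socioeconomic factors at baseline".

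Table 1, objective 3.2, states the analysis as "Relationship between participant characteristics* and weight outcome (24-weeks and 18-months". Neither this row nor section 3.3 gives the scale of the weight outcome. Section 3.3 anticipates general linear models for continuous outcomes and does not give adjustment terms model by model.

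Section 3.1 sets the BMI entry threshold at 28 kg/m² or more for non-Asian participants and 26 kg/m² or more for Asian participants. The thresholds are the same for men and women.

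**The concern.** Objective 3 asks for whom weight change is achieved, and section 4 intends the answers for tailoring and scaling the interventions. Two of the listed characteristics are tied to starting weight: ethnicity through the entry rule, and sex through height. Heavier people may lose more kilograms for the same proportional loss. In section 2 the continuous arm is a percentage energy restriction and the 5:2 arms aim for a comparable weekly restriction, which makes some scaling with body size plausible.

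If change is modelled in kg without baseline weight, a sex or ethnicity coefficient could therefore be nonzero even when every subgroup loses the same fraction of its weight. Section 3.3 then plans to use the qualitative themes to help explain associations found in the quantitative data, so a body-size difference could be given a behavioural explanation.

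**Working it through.** The article gives no sample size, power or effect size for these models, so there is no stated figure to reproduce. The check has three steps.

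**1. Entry rule and ethnicity.** Inputs from section 3.1: BMI thresholds 28 and 26. Assumed: height 1.60 to 1.80 m, and loss of 3% to 8% of baseline weight.

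Gap in minimum eligible weight = (28 − 26) × height². Apparent difference in loss = gap × proportional loss.

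| Height (m) | Minimum, non-Asian (kg) | Minimum, Asian (kg) | Gap (kg) | 3% | 5% | 8% |
|---|---|---|---|---|---|---|
| 1.60 | 71.7 | 66.6 | 5.12 | 0.15 | 0.26 | 0.41 |
| 1.70 | 80.9 | 75.1 | 5.78 | 0.17 | 0.29 | 0.46 |
| 1.80 | 90.7 | 84.2 | 6.48 | 0.19 | 0.32 | 0.52 |

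The apparent ethnicity difference is 0.15 to 0.52 kg. These are gaps in the minimum. They carry over to the means if BMI is spread alike above each threshold.

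**2. Height and sex.** Assumed mean heights: 1.76 m (men) and 1.63 m (women), with the same BMI in both.

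Gap in weight = BMI × (1.76² − 1.63²) = BMI × 0.4407.

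- BMI 28: 12.3 kg, or 0.37 to 0.99 kg of loss at 3% to 8%.
- BMI 36: 15.9 kg, or 0.48 to 1.27 kg of loss at 3% to 8%.

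**3. What the regression would show.** A least-squares simulation (400,000 people) had no true sex or ethnicity effect and loss equal to 3%, 5% or 8% of baseline weight. Further assumptions: 50% men, 20% Asian, the heights above, an ethnic height gap of 0 or 4 cm, the same BMI spread above each threshold, and residual SD 5 kg.

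| Model | Sex coefficient (men minus women) | Asian coefficient |
|---|---|---|
| kg, no baseline weight | −0.42 to −1.15 kg | +0.15 to +0.82 kg |
| kg, with baseline weight | within 0.03 kg of zero | within 0.03 kg of zero |
| Percent, with or without baseline weight | within 0.04 points of zero | within 0.04 points of zero |

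In the first row men appear to lose more and Asian participants less, although all lose the same fraction. With no ethnic height gap the Asian coefficient is +0.15 to +0.43 kg; a 4 cm gap raises it to +0.32 to +0.82 kg.

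**The case against.** **The list is not declared a closed adjustment set.** This stands. Section 3.3 names variables whose associations will be examined, calls the model types anticipated, and does not say whether the models are mutually adjusted. A fuller analysis plan may add terms, so exclusion of baseline weight is not proven. What remains is that the list appears in four places, baseline weight is absent from each as a predictor, and the outcome scale is not given.

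**The size depends on the kg scale.** This also stands, and it makes the point conditional. If percent change is analysed and loss is proportional, the artefact disappears without adjustment.

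**Adjustment may be the wrong target.** Body size is partly a consequence of sex and may lie on the path to weight change. The unadjusted contrast is a legitimate answer to the question of who loses weight; the adjusted contrast answers another (Lord's paradox). That is a reason to show both and label them, not to leave the choice unstated.

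**Stronger readings a reader might infer.**

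- *Confounding by centre, with occupation tied to site.* Section 3.1 implies more than one site ("for Asian men and women and be able to attend either study site"), and section 5 reports that "Ethical approval has also been obtained from the University of South Australia (HREC ID: 202379) and Ambulance Victoria Research Committee (R19-037"). The document does not list site among the evaluation's variables, say that dietitians differ by site, or show that ambulance staff cluster at one centre. No site effect can be computed.
- *A sex or occupation link built in by the entry rule.* The BMI thresholds are the same for both sexes and do not refer to occupation. Only ethnicity is linked by the rule.
- *A biased comparison of the diets.* Intervention group is randomised, so omitting baseline weight does not bias that comparison. At most it costs precision: with an assumed correlation of 0.2 to 0.5 between baseline weight and change, the residual variance forgone is r² = 4% to 25%.

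**Conclusion.** The point holds in conditional form. The predictors listed for the weight-change regressions leave out a baseline value that the evaluation holds, and the scale of the outcome is not fixed. If change is analysed in kg, the ethnicity association may carry about 0.15 to 0.52 kg from the entry rule alone, and the sex association about 0.37 to 1.27 kg from height. Both ranges rest on assumed heights, and on loss of 3% to 8% in proportion to baseline weight; the sex range also assumes equal BMI of 28 to 36. The only inputs the article supplies are the two BMI thresholds.

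The documents do not support saying that these associations are confounded, only that they may be. This is an inexpensive improvement to an exploratory analysis and does not affect the validity of the randomised comparison.

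**What to change.** In section 3.3, and in the Table 1 rows for objective 3:

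- State the scale of weight change, and report percent change alongside kg at 24 weeks and 18 months.
- Add baseline weight as a covariate in the weight-change models.
- Show the results unadjusted for baseline weight as well, and say which question each set answers: unadjusted, how change differs between the groups as enrolled; adjusted, how it differs between people of the same starting weight.

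Study site may be added as a covariate because there is more than one site, but this is optional.

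The cost is one model term and an extra set of results. Weight is already collected at baseline, 24 weeks and 18 months, so no new measurement is needed.

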## Discussion

4.

Night shift workers are at greater risk for obesity, type 2 diabetes, and cardiovascular disease (2, 3). There is limited guidance on what dietary interventions may be useful for weight management in this population group (7–8). It has been suggested that both energy restriction and meal timing may be needed to address circadian misalignment and to result in effective weight loss (10, 11). To explore this concept, the Shifting Weight using Intermittent Fasting in night shift workers (SWIFt) study is a world-first, randomized controlled trial (RCT) that compares three weight-loss interventions (11). While the SWIFt RCT will determine the *effectiveness* of these dietary interventions for weight-loss, this mixed-methods evaluation will provide an important step in determining for who the SWIFt interventions work best for, what intervention features are important, and what external factors may need to be addressed to strengthen an approach. The findings from this mixed-methods evaluation will be useful for tailoring any future scalability of the SWIFt dietary weight-loss interventions for night-shift workers.

## Ethics and dissemination

5.

This mixed-methods evaluation protocol was approved by Monash Health Human Research Ethics Committee (RES 19-0000-462A) and registered with Monash University Human Research Ethics Committee. Ethical approval has also been obtained from the University of South Australia (HREC ID: 202379) and Ambulance Victoria Research Committee (R19-037). Consent to participate in both the quantitative and qualitative parts of the study was sought before data collection. Personal information (name and contact details) will be collected by study researchers and stored separately to research data in a password protected electronic database. Only the study’s researchers will have access to this information. All methods will be performed in accordance with the relevant guidelines and regulations of the approving ethics committees. Results from this evaluation will be disseminated via peer-reviewed journals, conference presentations, student theses, and presentations to interested workplaces that include shift workers.

## Ethics statement

The studies involving humans were approved by Monash Health Human Research Ethics Committee. The studies were conducted in accordance with the local legislation and institutional requirements. The participants provided their written informed consent to participate in this study.

